	3. Transfer from another hospital
	4. More than 2000 ml intravenously administered fluid has been given (pre-hospital, in ED, or both)
	5. Likely requirement for immediate surgery
	6. Age < 18 years
	7. Pregnancy (confirmed or suspected)
	8. Patient in extremis or death deemed imminent and inevitable
	9. Patient wishes or comorbidities such that either fluid loading or vasopressor support is not considered clinically appropriate
Intervention	*Intervention arm*:
	Commence vasopressor infusion (± maintenance IV fluid) if SBP < 90 mmHg or mean arterial pressure (MAP) < 65 mmHg). Reassess hourly next 6 h and administer further 250-ml IV fluid bolus if required
	*Comparator arm*:
	Give a second 1000-ml fluid bolus plus further 500-ml boluses as clinically indicated until judged to be euvolaemic. Commence vasopressor infusion (± maintenance IV fluid) if SBP < 90 mmHg or MAP < 65 mmHg). Reassess hourly next 6 h and administer further 500-ml IV fluid bolus if required
Primary outcome measure	Total volume of intravenously administered fluid (including pre-randomisation) at 6 h
Secondary outcome measures	• Mortality (all-cause) at 90 days post enrolment
	• ICU length of stay
	• Hospital length of stay
	• Hospital-free days to day 90
	• Organ failure
	o Cardiovascular
	▪ Requirement for vasopressors
	▪ Duration of vasopressor requirement (h)
	▪ Vasopressor-free days to day 28
	o Respiratory
	▪ Requirement for ventilation (NIV/IPPV)
	▪ Duration of ventilator support (h)
	▪ Ventilator-free days to day 28
	o Renal
	▪ Requirement for renal replacement therapy (RRT)
	▪ Duration of RRT
	▪ RRT-free days to day 28
	▪ AKIN score to day 7
Laboratory/mechanistic outcome measures	Peak values, as well as patterns of expression over time (T0–T24), will be analysed for a range of biomarkers and compared between the groups including:
	• Atrial natriuretic peptide
	• Troponin
	• Inflammatory cytokines
	o IL-6, IL-10, resistin
	• NGAL (a biomarker of renal injury)
	• Endothelial cell activation biomarkers
	o sVCAM, sICAM, sE-Selectin, sFlt-1
	• Soluble markers of glycocalyx degradation
	o Heparan sulphate, syndecan-1, hyaluronan
Feasibility outcome measures	• Proportion of eligible patients enrolled
	• Randomisation errors
	• Compliance – protocol violations
	• Proportion with completely recorded data
	• Proportion with complete study blood sampling
Sample size	50 per arm/100 total

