##### Laboratory

Study blood sampling:Enrolment (T0), 3 h (T3), 6 h (T6) and 12–24 h (T24)Plasma and serum samples (total 5 ml) at each sampling time pointBlood gas (arterial or venous) including lactate and haemoglobin at each sampling time pointBlood samples should not to be taken during fluid-bolus administration and should be taken from the opposite arm from any maintenance fluid being administered

Samples will be centrifuged and the extracted sera/plasma divided into 500-μl aliquots and stored at −80 °C for subsequent batch analysis.

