### Statistical methods and sample size calculation

The primary outcome is the achievement of a minimum clinically significant relative difference of 33% in the total cumulative fluid volume administered until T6 (including pre-randomisation fluids). In the control arm of an Australasian, multicentre randomised controlled trial of early goal-directed therapy in septic shock, the mean total volume administered within the first 6 h was 4200 ± 2650 ml [32]. We aim to achieve a reduction of 33%, to a mean of 2800 ± 1800 ml over 6 h in the restricted-volume arm compared to the standard-care arm. This will require 43 participants in each group to achieve 80% power with *α* = 0.05. This pilot trial is not designed to have sufficient power to detect differences in secondary clinical outcomes.

The trial will also measure a range of biochemical markers. There is limited relevant data to inform sample size calculations for these analyses. Based upon feasible recruitment within a 12-month time period, a sample size of 100 is attainable. This will allow a margin of safety for achieving differences in the primary outcome. It will also enable the detection of differences between means of the two treatment groups of 55.6% of the standard deviation (or larger) for the measured biomarker, with 80% power and *α* = 0.05. This calculation is based upon a cross-sectional *t* test, not a repeated measures test (which affords additional power). As such, these calculations are conservative.

Baseline clinical and demographic data will be analysed using chi-square or Fisher’s exact test for categorical data, and the Wilcoxon rank-sum test for continuous data.

Where biomarkers are normally or log-normally distributed, linear mixed models with maximum likelihood estimation will be employed to analyse the pattern over time. Differences in the pattern of expression of each biomarker between the groups will be tested by the interaction of time and group in the model. Additional covariates will be added to adjust for treating centre, illness severity and comorbidities. For biomarkers with skewed distributions resistant to successful transformation, quantile regression with per-person cluster adjustment will be used.

A biostatistician will perform the statistical analysis.

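### Entered as patient-constant main effects, the planned biomarker covariates leave the tested time-by-group interaction essentially unchanged; modelling T3, T6 and T24 given T0 would use them

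*Protocol article*

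**What the plan says.** All the relevant wording is in the protocol article under Statistical methods and sample size calculation. For biomarkers that are normal or log-normal, "linear mixed models with maximum likelihood estimation will be employed to analyse the pattern over time". The tested effect is named: "Differences in the pattern of expression of each biomarker between the groups will be tested by the interaction of time and group in the model". The adjustment follows directly: "Additional covariates will be added to adjust for treating centre, illness severity and comorbidities". The text does not say whether the covariates enter as main effects only or also crossed with time, and it does not name the severity measure. There is a second model for the remaining biomarkers: "For biomarkers with skewed distributions resistant to successful transformation, quantile regression with per-person cluster adjustment will be used".

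Sampling, under Laboratory in Study measurements, is at "Enrolment (T0), 3 h (T3), 6 h (T6) and 12–24 h (T24"). The Clinical list in the same section collects the Charlson score, SOFA at admission and at 24 h, and the peak APACHE II score of the first 24 h. Randomisation is stratified by site (Screening and randomisation). Table 1 gives the sample size as "50 per arm/100 total" and lists "Proportion with complete study blood sampling" among the feasibility outcomes. The section Laboratory/mechanistic outcomes also plans a between-group comparison of peak values.

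**The concern.** The plan pairs one tested coefficient with an adjustment that, read plainly, acts on another. Centre and comorbidity are fixed for a patient, and so is severity if a single value is used. As main effects they move a patient's whole profile up or down. The interaction compares the arms on change within patients, from which any such shift drops out.

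The report would then show an adjusted interaction that is practically the unadjusted one. It would seem to allow for the stratification factor and for chance imbalance in severity, while doing neither for the effect under test. The biomarker study carries half of the trial's stated hypothesis and the mechanistic case for a larger trial. With 100 participants, unused precision is a real loss.

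**Working it through.** **1. The plan's own figure.** The article states a detectable difference of 0.556 SD with 80% power, from a cross-sectional t test with 50 per arm. Normal approximation, two-sided 5%: (1.960 + 0.842) × √(2/50) = 0.560 SD, and power at 0.556 SD is 0.794. The figure is reproduced and is not in dispute.

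**2. Why the covariates cancel.** For patient i at time j (j = 0 for T0), with arm g and patient-constant covariates x:

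Y_ij = α + β_j + γ·g_i + δ_j·g_i + θ·x_i + b_i + e_ij

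Y_ij − Y_i0 = β_j + δ_j·g_i + (e_ij − e_i0), with j = 0 as reference.

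Both θ·x_i and b_i drop out. With complete data the estimate of δ_j is the between-arm difference in mean change, whatever x contains.

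**3. Simulation.** 100 patients, 4 times, 8 sites, maximum-likelihood mixed model with categorical time, fitted with and without severity, comorbidity and site. Variances, covariate effects and missingness rates are assumptions, because the article gives none.

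| Setting | Change in interaction estimate | SE ratio, with/without covariates |
|---|---|---|
| Complete data, random intercept | at most 3e-14 | 1.000 |
| Complete data, random slope | at most 3e-14 | mean 1.000 (0.98–1.03) |
| 15% of post-T0 samples missing at random | mean 0.006–0.007, at most 0.025 | 0.999 |
| About 25% missing, related to severity | mean about 0.015, at most 0.058 | 0.993–0.997 |
| Severity and comorbidity also crossed with time, true severity-by-time effect 0.2 per visit | mean 0.047 | 0.90 |

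In the fourth setting the interaction Wald statistic changed by −12% to +25%. With complete data the same main-effect covariates moved the group main effect by 0.10–0.14 on average and cut its SE to 0.72–0.73. So they are informative, but for a coefficient that the plan does not test.

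**4. What conditioning on T0 gains.** With unit variance and correlation r between times:

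- change contrast at one time: variance proportional to 2(1 − r)
- contrast given T0: variance proportional to 1 − r²
- ratio: (1 − r²)/(2(1 − r)) = (1 + r)/2, that is 0.65, 0.75 and 0.85 at r = 0.3, 0.5 and 0.7.

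**5. Power.** Assume compound symmetry, complete data, a constant 0.556 SD effect at T3, T6 and T24, and 50 per arm. The noncentrality is 25 × 0.556² = 7.728, multiplied by:

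- 3-df time-by-group interaction: 0.75/(1 − r)
- joint 3-df group test given T0: 3/((1 − r)(1 + 3r))

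| r (assumed) | Interaction: noncentrality, power | Joint test given T0: noncentrality, power |
|---|---|---|
| 0.3 | 8.28, 67% | 17.43, 95% |
| 0.5 | 11.59, 83% | 18.55, 96% |

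These powers include no gain from site, severity or comorbidity. In one simulated fit with T0 in the model, adding covariates reduced the SE of the group effect from 0.134 to 0.113.

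**6. A limit on the remedy.** Step 2 applies equally among the post-T0 values: T0, site and the other covariates are again constant within a patient, so a group-by-time term among T3, T6 and T24 is left unchanged. In a complete-data fit of that model it was 0.296711 (SE 0.3013) both ways. The test has to be of the group effect at those times.

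**The case against.** The strongest reply is that the article never says main effects only. Covariate-by-time terms are not excluded, SOFA is recorded twice and could enter as time-varying, and a condensed article may leave functional form to an analysis plan that is not shown. That stands as a limit: the point is conditional on the plain reading. It does not remove the point, because the article itself chose both the test and the adjustment, and worded as they are the second does not act on the first.

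Three further objections also stand. Incomplete sampling is anticipated, so the two tests will not be exactly equal, and covariates that predict missingness have some use. Quantile regression is outside the algebra: in simulated median regressions the interaction coefficients moved by 0.18 on average, though some fits reached the iteration limit. The comparison of peak values is untouched, since there the covariates can act.

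A reader might infer that the adjusted and unadjusted analyses are always the same test, or that the document describes an adjustment it demonstrably does not perform. The documents do not support either, for the reasons just given. Nor should the factors 0.65 to 0.85 be read as the loss from inert covariates; they measure the gain from conditioning on T0. Finally, allocation is randomised, so the interaction test remains valid. These are exploratory outcomes in a pilot, and the primary outcome and sample size are unaffected.

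**Conclusion.** The point holds in conditional form. If centre, severity and comorbidity enter the linear mixed model as patient-constant main effects, the adjustment does nothing for the time-by-group test with complete data and very little with modest missingness. What is lost is efficiency and a correct description of what was adjusted, not validity. Under the assumptions of the power calculation, testing group at T3, T6 and T24 given T0 raises power from 67–83% to 95–96% for r between 0.3 and 0.5. The serial correlation is not in the article, so these figures are illustrative, and the advantage narrows as r rises. The extra gain from the covariates depends on how prognostic they prove to be. This should be changed before analysis, but it is not critical to the trial.

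**What to change.** For the mixed models, take T3, T6 and T24 as the outcomes. Include that patient's T0 value, site, and pre-randomisation severity and comorbidity as covariates. Test the group effect jointly at the three times and averaged over them, not by a group-by-time term among the post-T0 values. Severity should be a measure fixed before randomisation; the peak APACHE II score of the first 24 h and the 24 h SOFA extend beyond it.

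If the change-from-T0 interaction is kept as the target, state that the covariates are crossed with time, so that the adjustment reaches the tested effect.

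The cost is analysis wording only, since the samples and covariates are already planned. A rule is needed for patients with a missing T0 value. The target also shifts from change since T0 to post-T0 level given T0, and the text should say so.

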### Trial administration and Data Safety Monitoring Committee

Trial coordination will be by the Centre for Clinical Research in Emergency Medicine (CCREM) at the University of Western Australia, Perth, Australia. Case Report Forms will be completed by site investigators and sent electronically (after removal of individual patient identifiers) to the trial coordination centre for checking and data entry into a purpose-designed secure Research Electronic Data Capture (REDCap – Vanderbilt University, Nashville, TN, USA) database hosted by the University of Western Australia. Study blood samples will be processed at local hospital laboratories and stored for subsequent bulk shipping to the coordinating centre. All biomarker analyses will be performed in house at the CCREM laboratory facility in Perth.

The trial will be overseen by a Steering Committee, comprising site investigators from each participating site. The Steering Committee will meet monthly by teleconference. An independent Data Safety Monitoring Committee (DSMC) comprising an emergency physician, intensive care physician and biostatistician has been appointed to oversee the trial and will undertake periodic reviews at the discretion of the chair. The DSMC will review all deaths and adverse events (see below) and have the authority to suspend or halt recruitment if necessary. The DMSC will also assess relevant emerging published academic literature favouring one of the arms of the trial. Due to the small numbers precluding determination of any statistically significant difference in clinical outcomes between the arms, no formal interim analysis will be undertaken and no stopping rules are specified.

### Adverse events

Adverse events (AEs) are defined as any untoward medical occurrence in a patient administered an investigational intervention which does not necessarily require to have a causal relationship with this intervention.

Patients with severe sepsis in the ED and ICU commonly have aberrations in laboratory values, signs and symptoms due to the severity of their underlying disease and the impact of standard therapies [33]. These will not necessarily constitute an AE unless they require significant amelioration or are considered to be of concern in the investigator’s clinical judgment. AEs include all unexpected and/or untoward medical events experienced by the patient *which are not part of the expected course of sepsis*.

The following will be considered AEs, regardless of study treatment allocation and subsequent intervention required:Extravasation of peripherally administered noradrenaline infusion (whether or not any tissue injury occurred)CVC-related complicationsBleedingInadvertent arterial puncturePneumothoraxThrombosisInfectionArterial catheter-related complications, including thrombosisAny other event that is considered to be of concern by the site investigator

The AEs listed above will be recorded from the time of commencement of study treatment to 72 h post intervention. CVC-related complications, including infection, will be considered an AE for as long as the CVC remains in situ.

All AEs will be reported, irrespective of treatment allocation to the chief investigator and/or the REFRESH Management Committee and then forwarded to the chair of the DSMC.

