#### Standard treatment arm (see Additional file ***4***: Figure S3)

Management following randomisation after the initial 1000-ml fluid bolus for the next 6 h:Give a *second fluid bolus* of 1000 ml (balanced isotonic crystalloid)ReassessIf SBP ≥ 90 mmHg and MAP ≥ 65 mmHg give maintenance rate of 1–2 ml/kg/h (max 150 ml/h) via infusion pump, as clinically indicatedIf SBP < 90 mmHg or MAP < 65 mmHg:i.Give further *500-ml* boluses, at least every 30 min, until the treating clinician judges euvolaemia to be achievedii.Once euvolaemia is deemed present (e.g. inferior vena cava (IVC) non-collapsing on ultrasound, CVP > 8 mmHg, distended neck veins, etc.) and if the patient remains hypotensive:Start noradrenaline* infusion by peripheral IV route (large vein) and titrate to maintain MAP at 65–70 mmHgInsertion of urinary catheter and hourly urine output measuresInsertion of a central venous access (CVC/PICC) and commencement of central noradrenaline infusion once correct position confirmed by chest X-ray. Alternatively, at physician discretion and according to local protocol, if the anticipated duration of vasopressor requirement is less than 6 h the infusion can continue via a dedicated secure peripheral large venous cannula if the patient is monitored in a critical care environment and there is no other indication for central accessArterial line at the discretion of the treating clinicianTitration and weaning of vasopressors as per treating clinician and local protocolsAdditional therapies, e.g. vasopressin, corticosteroids at the treating clinician’s discretion

Reassess each hour for the first 6 h. At each reassessment consider the need for further fluid boluses based upon clinical assessment, including:Mental status, skin perfusionUrine outputRepeat lactate (if initially elevated)Ultrasound/echocardiography or CVP if available

If the treating clinician judges additional fluid to be required, administer an additional *500-ml* isotonic crystalloid IV bolus.

*An infusion of metaraminol via a peripheral IV cannula may be considered as an alternative to noradrenaline in accordance with local hospital policy.

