### Adverse event and serious adverse event reporting

Separate Case Report Forms will be developed to record AEs and SAEs. SAEs occurring from the time of commencement of study treatment to 72 h post intervention will be reported to the coordinating centre by faxing the supplied SAE Form within 24 h of site study staff becoming aware of the event. In this pilot trial, all deaths up to day 30 will be reported as a SAE. Coordinating centre staff will be responsible for following up SAEs to ensure that all details are available. It is the responsibility of each site to inform their Human Research Ethics Committee (HREC) of all SAEs which occur at their site, in accordance with local requirements.

All SAEs will be forwarded to the chair of the DSMC within 24 h of receipt at the REFRESH coordinating centre. As detailed in the Patient Information and Consent Form, any injury or complication occurring as a result of trial participation is to be reported to the study team who will arrange all necessary medical treatment. In Australia, Medicare will provide any required medical treatment, free of charge, in a public hospital.

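### Adverse-event recording lasts while the line is in place only for CVCs: arterial-catheter complications stop at 72 h and PICCs are not named, so capture of line harm differs by device in both arms

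*Protocol article*

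**What the plan says.** The Adverse events section lists what counts as an AE whatever the allocation. The list includes complications of CVCs and of arterial catheters, and ends with a catch-all for anything that worries the site investigator. Two sentences then set the recording period:

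- General rule: "The AEs listed above will be recorded from the time of commencement of study treatment to 72 h post intervention".
- Extension: "CVC-related complications, including infection, will be considered an AE for as long as the CVC remains in situ".

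No extension is given for arterial catheters, and the section does not mention PICCs.

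Under Study interventions, the pathways for both arms name CVC and PICC as the two forms of central access for noradrenaline, and both leave an arterial line to the clinician's discretion. In the standard arm this step comes after further boluses: "Once euvolaemia is deemed present" and the patient is still hypotensive.

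The serious-event rule has the same limit: "SAEs occurring from the time of commencement of study treatment to 72 h post intervention will be reported to the coordinating centre". The only stated exception is deaths, which are reported to day 30.

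**The concern.** The CVC sentence accepts that a line can cause harm for as long as it stays in, but the protocol applies this to only one of the three invasive lines it provides for. An arterial-line thrombosis on day 5 is the same kind of event as a CVC thrombosis on day 5, yet only the second has a stated place in the AE record. For the PICC the text leaves room for doubt: the intervention sections write CVC and PICC as two devices, and the AE section names one. Sites could reasonably differ on whether a PICC falls under the CVC rule.

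What is at stake is how complete and consistent the safety record is. Table 1 says the pilot is to assess safety as well as feasibility. The Data Safety Monitoring Committee works without stopping rules or a formal interim analysis and relies on its review of deaths and adverse events. Line harm that is counted differently by device is hard to summarise, and hard to carry into the design of the larger trial.

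**Working it through.** The plan states no figure on this point, so there is none to reproduce. The finding rests on the wording. The arithmetic shows only the possible size and direction.

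**Step 1. Recording period by device, as written**

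| Device | Named in AE section | Stated AE period | Non-fatal SAE period |
|---|---|---|---|
| CVC | yes | while in place | to 72 h |
| Arterial catheter | yes | to 72 h | to 72 h |
| PICC | no | to 72 h through the general AE definition or the catch-all; while in place only if CVC is taken to include it | to 72 h |

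The SAE route does not close the gap, because it also ends at 72 h except for deaths.

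**Step 2. Line time outside the window (assumed dwell times)**

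Assume a constant complication hazard, insertion at the start of the window, and a window of 72 h from the start of study treatment. For a dwell of D hours, the unobserved share is 1 − 72/D when D > 72, and 0 otherwise.

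- 72 h: 0
- 96 h: 1 − 72/96 = 25%
- 120 h: 1 − 72/120 = 40%
- 168 h: 1 − 72/168 = 57%

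If the 72 h run instead from the end of the 6 h study period, the window is 78 h and the last three become 18.75%, 35% and 53.6%.

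**Step 3. Does earlier insertion by itself bias the comparison?**

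For insertion at t hours, the captured share is min(D, 72 − t)/D. Take t = 1 h for the restricted arm and t = 3 h for the standard arm (both assumed).

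| Dwell | t = 1 h | t = 3 h |
|---|---|---|
| 48 h | 100% | 100% |
| 96 h | 71/96 = 74.0% | 69/96 = 71.9% |
| 120 h | 71/120 = 59.2% | 69/120 = 57.5% |
| 168 h | 71/168 = 42.3% | 69/168 = 41.1% |

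The arm with earlier insertion has slightly more of its line time inside the window, not less.

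**Step 4. Events missed per arm**

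Arm size comes from Table 1 ("50 per arm/100 total"). Assume a 10% complication risk per line, a 120 h dwell and the insertion times of step 3.

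- *Equal line use, 50% in each arm.* True events are 50 × 0.5 × 0.10 = 2.5 per arm. Missed events are 2.5 × (1 − 71/120) = 1.02 (restricted) and 2.5 × (1 − 69/120) = 1.06 (standard).
- *Unequal line use, 60% against 40%.* True events are 3.0 and 2.0, a difference of 1.00 and a ratio of 1.50. Counted events are 3.0 × 71/120 = 1.775 and 2.0 × 69/120 = 1.150, a difference of 0.625 and a ratio of 1.54. Missed events are 1.23 and 0.85.

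With equal use the two arms lose almost the same number. With unequal use the absolute difference shrinks while the ratio hardly moves. If lines come out within 72 h of the start of study treatment, nothing is missed in either arm.

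**The case against.** A reader might infer that the rule flatters the restricted arm, because that arm reaches vasopressors and lines sooner. The documents do not support this. The AE rule applies whatever the allocation. Both pathways offer the same devices, with the arterial line discretionary in the same terms. Both also let the infusion stay peripheral when vasopressors are expected to be needed for less than 6 h. Under a fixed window, earlier insertion slightly raises the share captured (step 3). A larger absolute loss in the restricted arm needs more lines or longer dwell there, and the protocol quantifies neither. This objection stands in full.

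A second inference would be that PICC complications go unrecorded altogether. That too goes too far. The section's general AE definition covers untoward events outside the expected course of sepsis, and the catch-all admits anything of concern, so a PICC complication within 72 h has a route in. Thrombosis and infection may also be separate list items rather than sub-items of the CVC entry; the list as available for this review does not settle it. CVC may simply have been meant to include a PICC. What remains is an ambiguity about PICC events after 72 h.

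Third, injuries or complications due to trial participation are to be reported to the study team, and that sentence has no time limit. But it concerns arranging treatment, turns on a judgement of cause, and sets no AE recording period.

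Finally, every dwell time, line-use rate and risk above is assumed, and AE counts are not among the listed outcomes. Both points are correct. They limit the importance of the finding but do not remove the inconsistency in the stated rule.

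**Conclusion.** The inconsistency is real and minor. As written, late non-fatal arterial-line complications have no recording period. The same applies to late PICC complications if CVC is read to exclude a PICC. The loss falls on both arms.

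Its size is unknown. It is nil if lines are removed within 72 h of the start of study treatment. Under the assumptions of step 2 it is 25% to 57% of line time for dwells of 4 to 7 days (18.75% to 53.6% on the longer reading of the window). The absolute difference between arms could be diluted only if line use or dwell differs between them. The documents show no bias in favour of the restricted strategy from earlier insertion. The primary outcome, fluid volume to 6 h, and the sample size are untouched.

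**What to change.** Replace the CVC-only extension in the Adverse events section with a sentence such as: complications of any CVC, PICC or arterial catheter, including thrombosis and infection, are recorded as AEs until that device is removed. Name the PICC in the list of device complications and on the AE form. Report device complications by randomised arm, over all randomised participants and among those who had the device. If CVC was always meant to include a PICC, say so.

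This changes recording only, not treatment. Sites already follow CVCs while they are in place and submit forms at the end of the hospital stay and at days 28 and 90, so the added burden is a few more AE entries for lines left in beyond 72 h. With 42 of 100 participants enrolled at submission, the amendment could still cover up to 58. Events in those already enrolled might be recoverable from the clinical record; any that are not should be noted when the results are reported.

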### Strategies to ensure protocol compliance and data integrity

Digital copies of de-identified Case Report Forms will be submitted electronically to the trial coordination centre at the following time points; enrolment, completion of hospital stay, 28 days and 90 days. This will allow for checking and data queries to be undertaken in a timely manner. This will also identify any protocol deviations and provide opportunity for feedback to the site investigator. A trained research assistant at the trial coordination centre will upload data into a secure trial database. There will be periodic internal audits of data accuracy and compliance.

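### A non-fatal central-line infection or thrombosis that first appears after line removal and after 72 h falls outside every stated safety window

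*Protocol article*

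**What the plan says.** The section on adverse events sets two windows. The general one is: "The AEs listed above will be recorded from the time of commencement of study treatment to 72 h post intervention". The list includes CVC-related complications, with thrombosis and infection among the items named, and an open-ended item for anything that worries the site investigator. The second window is specific to lines: "CVC-related complications, including infection, will be considered an AE for as long as the CVC remains in situ".

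The section on AE and SAE reporting sets the serious-event window: "SAEs occurring from the time of commencement of study treatment to 72 h post intervention will be reported to the coordinating centre". It adds one later element: "all deaths up to day 30 will be reported as a SAE". It also refers to the consent form, under which "any injury or complication occurring as a result of trial participation is to be reported to the study team", so that treatment can be arranged.

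The section on protocol compliance and data integrity says that Case Report Forms go to the coordinating centre at enrolment and then at "completion of hospital stay, 28 days and 90 days".

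**The concern.** Once 72 h have passed, only the in-situ rule is still open for line complications, and it closes when the line comes out. Infection and thrombosis can show themselves after that. A line may also be removed because one of them is suspected, in which case the event closes its own window. Extending the window beyond 72 h suggests that the authors thought 72 h too short for line harm. Ending it at removal gives part of that extension away.

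This matters because Table 1 states that the trial assesses the safety as well as the feasibility of a strategy built on early vasopressors, and central access follows from vasopressor use. The Data Safety Monitoring Committee has no stopping rules and works from its review of deaths and adverse events. An event that is never recorded as an AE has no defined route to it. The pilot's safety description is also meant to inform a larger trial.

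**Working it through.** The plan gives no figure on this point to reproduce. The check is to follow each kind of line complication through the stated windows.

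| Case | AE rule | SAE rule | Result |
|---|---|---|---|
| Appears within 72 h, line in or out | General window open | Open if serious | Recorded |
| Appears after 72 h, line still in | In-situ rule applies | Closed unless death by day 30 | Recorded as AE |
| Suspected after 72 h with line in, confirmed after removal | Depends on whether onset or confirmation decides; not stated | Closed unless death by day 30 | Unsettled |
| First appears after 72 h and after removal, non-fatal | Both windows closed | Closed | Not recorded |
| As above, but death by day 30 | Both windows closed | Death reported | Death recorded |

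**Other routes for the fourth case**

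1. The open-ended AE item is on the same list, so it has the same 72 h limit.
2. The SAE definition would cover an event that prolongs the hospital stay, but SAE reporting ends at 72 h.
3. The consent-form sentence has no time limit, but it concerns arranging treatment and sets up no AE record.
4. The clinical secondary outcomes contain no line infection or thrombosis. The process-of-care outcomes count how often and when CVCs are inserted, not their complications.

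No stated route records that case.

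**Direction between arms**

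The restricted arm reaches the vasopressor and central-access step when systolic pressure is below 90 or mean arterial pressure below 65 mmHg after the initial bolus. The standard arm first receives a second 1000 ml and, if still hypotensive, further 500 ml boluses. It reaches the same step "Once euvolaemia is deemed present" and hypotension persists. The background section on the alternative approach says that patients who respond to fluid may avoid vasopressors. More lines in the restricted arm are therefore plausible. The wording on central access, and on the peripheral alternative when vasopressor need is expected to last under 6 h, is the same in both arms.

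**Why the size cannot be derived**

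Let pR and pS be the proportions receiving a CVC, with 50 participants per arm, one line each and independent events. Let q be the chance per line of a complication of the fourth kind, equal in both arms. All three values are assumptions; the documents give none.

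- Expected loss = 50 × (pR + pS) × q
- Chance of losing at least one = 1 − (1 − q)^(50pR + 50pS)
- Restricted-arm share of the loss = pR / (pR + pS)

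Results:

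- Low end, pR = pS = 0.30, q = 0.01: 30 × 0.01 = 0.30 events; 1 − 0.99^30 = 0.26; share 50%.
- High end, pR = 0.60, pS = 0.30, q = 0.05: 45 × 0.05 = 2.25 events; 1 − 0.95^45 = 0.90; share 67%.
- Other splits: 0.40 v 0.30 gives a share of 57%; 0.50 v 0.20 gives 71%.

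The spread is set by what is put in, so these figures illustrate the range and do not estimate the loss.

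**Effect on the main analysis**

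The primary outcome is fluid volume to 6 h, and its sample size rests on means and standard deviations of that volume. No AE window enters either.

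**The case against.** The strongest reply is that the in-situ sentence widens safety capture. In the first 72 h every listed AE is recorded, whether or not a line is in place, and the sentence only adds time. A fatal line complication is still captured to day 30. The article condenses a fuller protocol and says that separate AE and SAE forms will be developed, so onset and attribution rules may sit there. These points stand and narrow the gap, but they do not close it: the article states an end-point for the window, and the case of first appearance after both limits falls outside it.

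A reader might infer three stronger things that the documents do not support.

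- **That a line removed on day 4 for fever, with a positive culture on day 5, is lost.** The complication showed itself while the line was in, so on an onset reading it counts. The text leaves this open; it does not exclude the case.
- **That the losses fall mostly in the restricted arm and make that strategy look safer than it is.** Reaching the vasopressor step sooner does not by itself mean more lines or more late events. CVC use is an outcome still to be measured, the recording rule is the same in both arms, and equal CVC rates with equal risk per line split the loss evenly.
- **That the lost events are the more serious ones.** Nothing in the article says so.

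It is also fair to say that 50 participants per arm would give an imprecise estimate of line harm even with perfect capture. That limits what the fix can achieve, but it does not justify leaving known complications unrecorded.

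**Conclusion.** The point holds in a narrow form. As written, a non-fatal line-related infection or thrombosis that first appears after removal and after 72 h is recorded neither as an AE nor as an SAE. One suspected in situ and confirmed after removal is left to each site's interpretation. This follows from the text alone.

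The effect is some under-counting of line harm in both arms. It is plausibly greater in the restricted arm if that arm receives more lines, but that condition is an assumption. The size of the loss cannot be derived. The primary outcome and the power calculation are unaffected. This is a cheap improvement to the safety record of a pilot.

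**What to change.** In the section on adverse events, state that CVC-related complications are recorded while the CVC is in situ, and that CVC-related infection or thrombosis is also recorded when it is diagnosed after removal, up to completion of the hospital stay. This settles the onset-or-confirmation question for those two complications within the hospital stay. Collect the dates of line insertion, removal, onset and diagnosis on the Case Report Form already submitted at that point. In the section on AE and SAE reporting, apply the same window to CVC-related SAEs; otherwise a serious late line complication would be an AE but not a reportable SAE.

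The cost is a sentence in each of the two sections and a few date fields, with no new visit and no change to patient care. The downside is slightly more recording and a few ambiguous attributions after removal. Events first diagnosed after discharge would still be missed, and the text should say so.
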